## Abstract

**Background:**

An abdominal aortic aneurysm (AAA) is a focal dilation of the abdominal aorta and is associated with a risk of fatal rupture. Experimental studies suggest that myo-inositol may exert beneficial effects on AAAs through favourable changes to biological pathways implicated in AAA pathology. The aim of the Inositol in the MAnaGemENt of abdominal aortic aneurysm (IMAGEN) trial is to assess if myo-inositol will reduce AAA growth.

**Methods/design:**

IMAGEN is a multi-centre, prospective, parallel-group, randomised, double-blind, placebo-controlled trial. A total of 164 participants with an AAA measuring ≥ 30 mm will be randomised to either 2 g of myo-inositol or identical placebo twice daily for 12 months. The primary outcome measure will be AAA growth estimated by increase in total infrarenal aortic volume measured on computed tomographic scans. Secondary outcome measures will include AAA diameter assessed by computed tomography and ultrasound, AAA peak wall stress and peak wall rupture index, serum lipids, circulating AAA biomarkers, circulating RNAs and health-related quality of life. All analysis will be based on the intention-to-treat principle at the time of randomisation. All patients who meet the eligibility criteria, provide written informed consent and are enrolled in the study will be included in the primary analysis, regardless of adherence to dietary allocation.

**Discussion:**

Currently, there is no known medical therapy to limit AAA progression. The IMAGEN trial will be the first randomised trial, to our knowledge, to assess the value of myo-inositol in limiting AAA growth.

**Trial registration:**

Australian New Zealand Clinical Trials Registry, ACTRN12615001209583. Registered on 6 November 2015.

**Electronic supplementary material:**

The online version of this article (doi:10.1186/s13063-017-2304-x) contains supplementary material, which is available to authorized users.

## Background

Abdominal aortic aneurysm (AAA) is a focal dilation of the abdominal aorta with a maximum diameter ≥ 30 mm [1]. The most recognised complication of AAA is aortic rupture, the risk of which increases at larger diameters [1, 2]. Patients with AAA have at least a twofold increased rate of cardiovascular events, particularly myocardial infarction, compared with individuals with normal aortic diameter [3]. AAAs can be readily identified when they are small by ultrasound surveillance or incidental imaging. At this stage, patients have minimal risk of AAA rupture and can thus potentially be treated early [4–7]. There are, however, limited current means to effectively treat such patients [1, 8, 9]. The only treatment currently available for AAA is surgical repair, which is associated with significant mortality (1–5%), peri-operative complications, in-hospital costs, and the need for post-operative follow-up, imaging and, in some cases, repeat surgery [1, 5, 7, 10–12]. Four randomised controlled trials have demonstrated that early elective surgery does not reduce mortality for patients with small (<55 mm) AAAs [4–7]. It is estimated that 50–70% of small AAAs will eventually grow to a size at which surgical repair is indicated [5, 7, 13]. Effective medical therapies administered to patients with small AAAs could prevent or limit AAA growth, thereby reducing or avoiding the need for surgery. Only a small number of randomised controlled trials have been carried out to assess medical therapies for AAA, and none have identified an effective treatment [8, 9, 14]; however, a number of such trials are ongoing [15].

Findings from previous studies suggest that increased consumption of myo-inositol has the potential to target key pathways implicated in AAA progression [16–19]. Myo-inositol can be ingested from a number of foods and is found in high concentrations in vegetables, nuts, whole grains and fresh fruits [20]. Consumption of these foods has been associated with reduced prevalence of AAA and reduced incidence of cardiovascular events [21, 22]. Myo-inositol is a key component of the cell membrane structure and cell signalling pathways [23–25]. Myo-inositol and its metabolites play an important role in the control of cell proliferation, cell survival, matrix remodelling and inflammation [23–31]. Inositol phosphates have been shown to inhibit nuclear factor kappa-light-chain-enhancer of activated B cells (NF-κB) activation, which is recognised as a master regulator of inflammation and matrix remodelling [26]. Activation of NF-κB upregulates chemokines such as C-C motif chemokine 22 (CCL22), matrix metalloproteinases (MMPs) and cathepsins, which are all implicated in AAA pathogenesis [32–37]. Inhibition of NF-κB has previously been demonstrated to inhibit AAA growth in pre-clinical animal models [33, 36–38]. Inositol phosphates also control the mechanistic target of rapamycin (mTOR) signalling pathway [39]. Inhibition of mTOR limits AAA growth in pre-clinical rodent models by reducing aortic recruitment of inflammatory cells and inhibiting production of pro-inflammatory cytokines [40, 41]. Inositol phosphates have also been shown to favourably influence the production of bone proteins [42]. It has previously been reported that bone proteins, including osteoprotegerin (OPG), osteopontin (OPN) and sclerostin (SOST), are implicated in the pathogenesis of AAA [34, 35, 43, 44]. Collectively, these data suggest that myo-inositol has potential ability to limit key pathological mechanisms involved in AAA, although the effect of myo-inositol administration on AAA growth has not previously been assessed.

Dietary supplementation with myo-inositol has previously been examined in a number of patient groups, including women with polycystic ovary syndrome and gestational diabetes, as well as patients with depression, with favourable results [16, 17, 19, 45, 46]. Administration of doses of ~ 4 g per day has been reported to reduce circulating concentrations of pro-inflammatory cytokines such as resistin, as well as to favourably modify circulating lipids by reducing triglycerides and raising high-density lipoprotein (HDL) cholesterol and phosphatidylcholine plasmalogen lipids [16–19]. It has previously been reported that patients with AAA have a distinct circulating pro-inflammatory and lipid profile [47–50]. AAA is associated with high serum resistin, triglycerides, linoleic acid-containing triacylglycerols and diacylglycerols, and low serum HDL cholesterol [47–50]. Given the ability of myo-inositol to reduce inflammation and favourably modify the lipid profile in other patients, it is possible that this approach could have similar effects in patients with AAA. Such effects would be expected to limit the main complications in these patients, specifically AAA growth and cardiovascular events.

The primary aim of the Inositol in the MAnaGemENt of abdominal aortic aneurysm (IMAGEN) trial is to determine if dietary supplementation with 2 g of myo-inositol twice daily limits AAA growth over 12 months, evidenced by limiting AAA volume assessed on the basis of computed tomography (CT). The secondary aims of the IMAGEN trial are to examine the effect of dietary supplementation with 4 g of myo-inositol daily for 12 months on (a) AAA growth assessed by aortic diameter measured by CT and ultrasound; (b) AAA peak wall stress (PWS) and peak wall rupture index (PWRI) estimated on the basis of CT; (c) lipid profile; (d) circulating markers of inflammation, matrix remodelling and circulating RNA profile; and (e) health-related quality of life.

## Methods/design

### Study design

IMAGEN is a multi-centre, prospective, parallel-group, randomised, double-blind, placebo-controlled trial designed to assess if dietary supplementation with 2 g of myo-inositol twice daily for 12 months will reduce AAA growth. The trial will be conducted at four sites in Australia: The Royal Brisbane and Women’s Hospital, Brisbane; Gosford Vascular Services, Gosford; The Townsville Hospital, Townsville; and Mackay Base Hospital, Mackay. This trial protocol is reported according to the Standard Protocol Items: Recommendations for Interventional Trials (SPIRIT) (*see* Additional file 1). Only research personnel who are directly involved in the recruitment and data collection aspect of the study will have access to participants’ personal details. All case report forms (CRFs), source documentation and samples will be de-identified and coded with a study number, according to good clinical practice (GCP) guidelines.

### Participants

The IMAGEN trialists plan to enrol 164 participants who have an asymptomatic infrarenal AAA measuring a maximum diameter ≥ 30 mm on the basis of CT or ultrasound, both of which will be performed as part of the baseline assessments (see Fig. 1). Participants will be included only if they have a high likelihood of treatment compliance over 12 months as determined by their treating physician or local study coordinator. IMAGEN will not include patients with an existing indication for AAA repair or expectation that this will be revised within 12 months. Additional exclusion criteria include previous reaction to myo-inositol supplementation, inability to tolerate abdominal imaging, inability to provide blood samples and previous abdominal aortic surgery. A full list of inclusion and exclusion criteria is given in Table 1.

**Fig. 1 Fig1:**
[figure not shown]
Standard Protocol Items: Recommendations for Interventional Trials (SPIRIT) figure: schedule of enrolment, interventions, and assessments. *ABI* Ankle-brachial index, *BP* Blood pressure, *CT* Computed tomography

**Table 1 Tab1:** Patient eligibility criteria

Inclusion criteria
• Ability to provide written informed consent
• Diagnosis with an infrarenal AAA measuring a maximum diameter ≥ 30 mm based on CT or ultrasound
• No current indication for AAA repair according to the treating physician or expectation that this will be revised over 12 months
• High likelihood of treatment compliance over 12 months according to the treating physician and local study coordinator
• Aged ≥ 50 years
Exclusion criteria
• Symptomatic, ruptured or mycotic AAA
• Contraindication to the study protocol:
○ Previous reaction to myo-inositol supplementation
○ Inability to tolerate abdominal imaging
○ Inability to provide blood samples for safety and outcome analysis
• Previous abdominal aortic surgery
• Current or planned participation in another randomised trial
• Treating physician feels the patient is not suitable for trial entry

*CT* Computed tomography, *AAA* Abdominal aortic aneurysm

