### Interventions

Participants in the intervention group will receive four 500-mg capsules of myo-inositol, which is to be taken orally at 08:00 and 20:00 daily. This dose has been used in previous clinical trials in other patient groups and is well tolerated over 12 months, with no side effects reported [16–19, 45]. Furthermore, this dose has been reported to favourably modify lipid profile and reduce circulating concentrations of pro-inflammatory cytokines in other patient groups [16–19, 45], effects that would be expected to limit AAA growth [1, 8, 51]. Participants will be instructed to avoid ingesting aperients or coffee within 1 h of taking the study supplement because these may interfere with myo-inositol absorption [52]. Participants in the control group will receive four 500-mg capsules of inert cellulose powder, which is to be taken orally at 08:00 and 20:00 daily. It will be packaged in an identical fashion to the intervention drug by Pharmaceutical Packaging Professionals (Thebarton, Australia), an established current good manufacturing practice facility.

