#### Health-related quality of life

Health-related quality of life will be assessed using the 36-item Short Form Health Survey (SF-36) completed at 0, 6 and 12 months and has previously been validated for use in patients with AAA [69]. Additional outcome measures include dietary analysis assessed by means of a food frequency questionnaire and 24-h recall interview at baseline and at 6 and 12 months, as previously described [70]. Finally, acute cardiovascular events, requirement for peripheral arterial intervention, AAA rupture, all-cause mortality, changes in background medication and withdrawal from the study dietary supplement (by indication) will be recorded. These data will be recorded through patient interview every 6 months, chart reviews and linked data, as previously described [71–73].

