### Sample size and power calculations

It is hypothesized that dietary supplementation with 4 g of myo-inositol daily for 12 months will reduce AAA growth by 40%, as evidenced by limiting increase in AAA volume from 8.1 ± 6.9 cm^3^ to 4.9 ± 6.9 cm^3^. Estimated outcomes for the control group are based on CT volume measured in a pilot cohort [53]. An effect size of 40% is based on the consideration of outcomes likely to be required for clinical efficacy. For example, if myo-inositol reduced annual increase in AAA size by 40%, the estimated time for an AAA initially measuring 40 mm to reach the commonly employed intervention level of 50 mm would be increased from 5 to ~ 7 years. Given that the annual mortality rate due to non-AAA-related causes is ~ 5% in patients with small AAAs, this reduction in growth could be expected to result in ~ 10% less patients requiring interventions over 5 years. This has significant potential social and economic benefit, with a possible cost saving of ~ $1 million per year [5, 6, 12]. On the basis of these estimated outcomes, 74 participants per group are required (80% power, α = 0.05) to detect the hypothesized reductions in AAA volume. Using data from a pilot cohort, it is estimated that this sample size will have a power of ~ 85% to detect a 40% reduction in orthogonal AAA diameter increase, assuming that the SD for the intervention group reduces in line with the mean. Allowing for a dropout rate of 10%, a total of 164 patients will be required. Sample sizes were calculated using G*Power 3.1 software.

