## Discussion

One of the main risk factors for AAA is age, with the problem being much more common in the > 60-year-old age group [1, 8]. With the continued expansion in the elderly population, the number of AAA operations can be expected to continue to increase [78]. Alternative forms of treatment for AAA are urgently needed, ideally those which are non-invasive, suitable for the older age group and cost-effective. The IMAGEN trial will be the first randomised trial, to our knowledge, to assess the value of myo-inositol in limiting AAA growth. To date, only two trials of medical treatment of AAA with sufficient sample size have been published, and both had negative findings [9, 79]. If the present hypotheses are confirmed, it is estimated that myo-inositol could lead to a reduction in AAA surgery of ~ 1–2% per year at the expense of a low-cost dietary supplement. The results of this trial could markedly change the clinical management of small AAAs, which currently consists of ultrasound surveillance. This study will also provide important information on (a) biomarkers which predict responsiveness to myo-inositol, (b) the effect of myo-inositol on cardiac events and (c) biomarkers for AAA growth. The IMAGEN trial may identify circulating markers which can be used to guide management of small AAA and selection for therapy by drugs or surgical interventions.

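### The eligibility criteria do not exclude people already taking a myo-inositol supplement, so some placebo participants could be on the test substance; the loss of power is probably small and one added criterion prevents it

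*Protocol article*

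**What the plan says.** The Participants section closes with "A full list of inclusion and exclusion criteria is given in Table 1", so the table is offered as complete rather than as a summary. In Table 1 the one entry that mentions the test substance is "Previous reaction to myo-inositol supplementation", listed among the contraindications to the study protocol. No entry concerns current or recent use. The broadest exclusion is "Treating physician feels the patient is not suitable for trial entry", which is left to judgement and does not mention supplements.

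Under Interventions, the one intake restriction given is "Participants will be instructed to avoid ingesting aperients or coffee within 1 h of taking the study supplement". The Discussion describes the product as a treatment available "at the expense of a low-cost dietary supplement", and the Background notes that it also occurs in ordinary food: "Myo-inositol can be ingested from a number of foods and is found in high concentrations in vegetables, nuts, whole grains and fresh fruits".

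Diet is recorded: "Additional outcome measures include dietary analysis assessed by means of a food frequency questionnaire and 24-h recall interview at baseline", and again at 6 and 12 months. The same section says that changes in background medication are recorded. Neither record is used for eligibility.

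The Data analysis section analyses participants by intention to treat. The sample size section plans on "limiting increase in AAA volume from 8.1 ± 6.9 cm^3^ to 4.9 ± 6.9 cm^3", with 74 per group.

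**The concern.** A criterion that removes only those who reacted to myo-inositol leaves in those who take it without trouble. Such a person satisfies every line of Table 1 and can be allocated to placebo. During follow-up this participant is exposed to the substance under test but is counted in the control mean, because the analysis follows allocation.

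If myo-inositol slows growth, these participants pull the control mean down towards the treated mean, and the trial estimates a smaller difference than the one it was sized for. The sample size allows only for 10% dropout, with nothing for exposure in the control arm. The interim analysis also bases its futility assessment on observed growth, so a diluted difference would feed into that decision too.

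**Working it through.** **Inputs (protocol article, sample size section)**
- Mean 12-month volume increase: 8.1 cm³ in control, 4.9 cm³ on treatment; difference 8.1 − 4.9 = 3.2 cm³.
- SD 6.9 cm³ in both groups.
- 74 per group, 80% power, α = 0.05. Sidedness is not stated.
- Dropout 10%, total 164.

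**Step 1: reproduce the plan's figure.** Two-sample t test with noncentral t power:
- Standard error of the difference = 6.9 × √(2/74) = 1.134.
- Noncentrality = 3.2 / 1.134 = 2.82, on 2 × 74 − 2 = 146 degrees of freedom.
- Two-sided critical value at 0.05 = 1.976.
- Power = 80.0%. The smallest n per group that reaches 80% is 74, as stated. (The normal approximation gives 73 two-sided and 58 one-sided, so the plan used a two-sided test.)
- Total: 148 / 0.9 = 164.4, consistent with 164.

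**Step 2: model of dilution.** Let q be the share of placebo participants who take their own myo-inositol at an effective amount throughout.
- Users on placebo grow at the treated rate, so the control mean becomes 8.1 × (1 − q) + 4.9 × q = 8.1 − 3.2q.
- Users allocated to myo-inositol also grow at the treated rate, so the active mean stays at 4.9.
- Expected difference = (8.1 − 3.2q) − 4.9 = 3.2 × (1 − q).

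The SD is held at 6.9.

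**Step 3: power at 74 per group.** The values of q are assumptions; the article gives none.

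| q | Difference (cm³) | Power | n per group for 80% |
|---|---|---|---|
| 0% | 3.20 | 80.0% | 74 |
| 1% | 3.17 | 79.2% | 76 |
| 2% | 3.14 | 78.4% | 77 |
| 5% | 3.04 | 75.9% | 82 |
| 10% | 2.88 | 71.3% | 92 |

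**Step 4: lower intake.** If users obtain only a fraction f of the effect, the difference is 3.2 × (1 − fq). With f = 0.5 and q = 10% this is 3.2 × 0.95 = 3.04 cm³, the same as 5% full users, with power 75.9%.

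**Step 5: with the exclusion in place.** If no placebo participant takes myo-inositol, q = 0, the planned 3.2 cm³ stands, and 74 per group is unchanged.

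**The case against.** The best case on the other side is that nothing in the article suggests that patients with aneurysms take this supplement. Its account of earlier use concerns women with polycystic ovary syndrome or gestational diabetes and patients with depression, whereas this trial enrols people aged 50 or over with an aneurysm. The previous-reaction entry reads as a safety exclusion and is no evidence that users are expected. The trial dose is 4 g daily, and lower personal intake would dilute less. The treating physician can also turn away a known user. All of this stands as an argument about size: at 1–2% users the loss is about one to two points of power. It does not close the gap, because the physician's criterion is discretionary and the list is declared complete.

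The lack of an instruction against off-trial use is a weaker point. The article calls only the eligibility list full. Other participant instructions may sit in the full protocol or participant information, which are not shown, so their absence here is not counted.

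Two stronger readings are tempting, and the document does not support either:
- A reader might infer that users in the active arm dilute the contrast as well. The endpoint is growth over 12 months, and under the model such a person still grows at the treated rate. The dilution comes from placebo users.
- A reader might infer that a null result could not be separated from contamination. The food frequency questionnaire, the 24-hour recall and the record of medication changes do not name supplements, but they give some route to detecting use.

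Nor can anything be built on what participants learn at consent, since the consent material is not available.

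**Conclusion.** The gap holds: by a list declared complete, a current user who tolerates myo-inositol is eligible and may be allocated to placebo. The consequence is a bias of the primary difference towards zero, from 3.2 to 3.2 × (1 − q) cm³. Power falls from 80.0% to between 79.2% and 71.3% for assumed user shares of 1% to 10%.

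This rests on three assumptions: the treatment works, users' own intake is near an effective amount, and the share of users is within the range shown. The article supports no particular share, and it may be low. The sample size figure is not in error and nothing in the article contradicts itself here. This is an inexpensive design improvement of uncertain but probably modest size. It is not a flaw that would invalidate the result.

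**What to change.** Add one exclusion to Table 1: current use of a myo-inositol-containing supplement at screening. Whether a washout is needed, and how long, is for the investigators to decide.

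Unless the full protocol already does so, add a question on off-trial myo-inositol use to the contacts already scheduled (calls at 1, 3 and 9 months, visits at 6 and 12 months). As the article reports that recruitment is under way, the question would also identify use among participants already enrolled.

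The cost is one line in the criteria and one question at existing contacts, with no change to the sample size. The downside is that a few current users cannot be enrolled. If they turn out to be more than a few, recruitment would feel it, but the dilution avoided would be correspondingly larger.

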### Randomisation

The randomisation scheme will be generated from Stata code (StataCorp, College Station, TX, USA) and maintained by the central clinical trial pharmacist. Randomisation to myo-inositol or placebo will be stratified by study centre, presence of diabetes and aortic diameter (30–34, 35–39, 40–44, 45–49 and ≥ 50 mm) as measured on ultrasounds. Randomisation will be blocked in a 1:1 ratio (randomly to a maximum block size of 8). The central and site trial managers will be blinded to treatment allocation. Eligible and consenting participants will be allocated to inositol or placebo groups via a telephone call. Once an allocation number is obtained, the trial supplement will be dispensed by the local clinical trial pharmacist (after randomisation and at the 6-month time point). Allocation concealment will be achieved by using a central randomisation centre and employing identical packaging of intervention and placebo. Participants, investigators and outcome assessors will be blinded to treatment allocation. In the case of an emergency where breaking of the group allocation blinding is required, the local study centre clinical trial pharmacist will be contacted.

